### Study objectives

The primary objective of the study is to assess the incidence and risk factors of post-COVID-19 condition in a cohort of recovered COVID-19 patients.

The secondary objectives of the study are as follows:To evaluate the association between circulating SARS-CoV-2 variants and the risk of post-COVID-19 condition.To identify different clinical phenotypes of post-COVID-19 condition.To evaluate the long-term residual organ impairment, specifically of the lung, heart, central nervous system, and peripheral nervous system, in relation to patient demographic and clinical characteristics such as age, gender, comorbidities, severity of disease, and virology including viral variant, specific mutations, and viral load in the acute phase.To compare the incidence of post COVID-19 condition between males and females.

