### Patient assessment and follow-up protocol

The patient assessment and follow-up protocol for acute COVID-19 disease involves follow-up visits at 2–3, 6–9, and 12–15 months after clinical recovery. At each visit, routine blood exams and medical visits will be conducted, along with several assessments via questionnaires, including the short version of the post COVID-19 WHO Case Report Form (WHO CRF) for collection of symptoms and newly emerged complaints after COVID-19, the Fatigue Numerical Rating Scale, the Medical Research Council (MRC) dyspnoea scale, the 5-level EQ-5D test (EQ5D-5L), the 12-item WHO Disability Assessment Schedule (WHODAS), the Montreal Cognitive Assessment (MOCA), the Hospital Anxiety and Depression Scale (HADS-A/D), and a screening tool named PCL-5 for Post-Traumatic Stress Disorder (PTSD). If patients are unable to attend the post-COVID-19 clinic, the questionnaires will be able to be completed through a phone interview. All questionnaires will be standardized and available in multiple languages (Fig. 1).

Further instrumental diagnostic evaluations such as diffusing capacity of lung carbon monoxide (DLCO), spirometry, lung computed tomography (CT) scans, pneumological evaluation, echocardiography, cardiological evaluation, neurological evaluation, rehabilitation medicine specialist examination, and psychological evaluation will be conducted as necessary.

Pulmonary symptoms are common after the acute phase, thus patients undergo the MRC dyspnoea scale and oxygen saturation measurement at each post-COVID visit. Further evaluations such as chest CT scans, diffusing capacity of lung carbon monoxide (DLCO), spirometry, and a complete pneumological evaluation will be performed if oxygen saturation is < 95% or MRC dyspnoea scale grade is 2–5.

Patients who recovered from acute COVID-19 disease could present a higher risk of cardiac diseases, including heart failure, myocardial infarction, and arrhythmia in the mid- and long-term [18]. During the scheduled post-COVID visits, patients undergo a complete medical examination, including heart rate and blood pressure measurement, and fill in the MRC dyspnoea scale. Further evaluations such as an electrocardiogram, a cardiologic visit, and an echocardiography will be performed as necessary.

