Neurocognitive and neuropsychiatric sequelae are important to investigate for their great impact on patients’ quality of life [6, 19, 20]. Neurocognitive and neuropsychological performance will be assessed by questionnaires, including the previously mentioned HADS-A/D, PCL-5, and MOCA, which will be performed at each scheduled visit. Patients will be referred to a psychologist or a neurologist as necessary (Table 1).

**Table 1 Tab1:** Displaying the specific assessments to be conducted at each study time point

Study Flowchart				
**Procedures**	**At acute phase**	**At T1 (2–3 months)**	**At T2 (6–9 months)**	**At T3 (12–15 months)**
Nasopharyngeal swab	X			
Demographic/clinical data collection	X			
Routine blood tests		X	X	X
Blood/serum samples collection		X	X	X
Medical visit, oxygen saturation (SO2) measurement		X	X	X
Symptoms assessment (WHO CRF)		X	X	X
Fatigue Numerical Rating and Severity Scale		X	X	X
Modified MRC Dyspnoea Scale		X	X	X
Hospital re-admission, relapse or new comorbidity		X	X	X
COVID-19 vaccination status		X	X	X
QoL (EQ5D-5L)		X	X	X
Montreal Cognitive Assessment (MOCA)		X	X	X
Psychological questionnaires (HADS-A/D, PCL-5)		X	X	X
WHODAS questionnaire		X	X	X
If abnormal SO2, DLCO		X		X
If abnormal SO2, spirometry		X		X
If abnormal SO2 and/or clinically indicated, pneumology visit		X	X	X
Electrocardiogram (ECG)		X		
If cardiac symptoms, echocardiogram		X		X
If cardiac symptom and/or clinically indicated, cardiology visit		X	X	X
If abnormal psychological questionnaires and/or clinically indicated, psychology evaluation		X	X	X
If abnormally MOCA and/or clinically indicated, neurology visit		X	X	X
If abnormally WHODAS and/or clinically indicated, rehabilitation medicine visit		X	X	X

Legend: T1, T2 and T3: post COVID-19 visit at 2-3 months, 6-9 months and 12-15 months after clinical recovery.

Blood/serum samples collection: whole blood samples will be stored, centrifuged, and separated into plasma and peripheral blood mononuclear cells for immunological and viral analyses

WHO CRF, WHO’s Post COVID case report form; MRC dyspnoea scale, Modified Medical Research Council Dyspnoea Scale; QoL (EQ5D-5L), quality of life (5-level EQ-5D version); MOCA, Montreal Cognitive Assessment; HADS-A/D, Hospital Anxiety and Depression Scale; PCL-5, Post Traumatic Stress Disorders (PTSD) checklist for DSM-5; WHODAS, World Health Organization Disability Assessment schedule 2.0, 12-item version; DLCO, Diffusing capacity of the lung for carbon monoxide test

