### Questionnaires administration

The fatigue numerical rating scale will be used to assess the severity of fatigue experienced by patients, while the MRC dyspnoea scale will be used to evaluate breathlessness. Quality of life will be assessed using the EQ5D-5L tool, which consists of the EQ-5D descriptive system and the EQ visual analogue scale (EQ-VAS). The HADS will be used to evaluate symptoms of anxiety and depression, while the PCL-5 will be used for first screening for PTSD and monitoring symptoms change during time. The MOCA will be used to assess cognitive function, and the WHODAS 2.0 will be used to measure health and disabilities in clinical practice. All questionnaires with the relative scores and the CRF will be listed in Table 2 and more detailed information attached as supplementary documents (Supplementary Appendix).

**Table 2 Tab2:** Presenting the questionnaires administered to enrolled patients, along with information regarding their scoring

Administered questionnaires	
**Score**	**Levels/range**
Symptom assessment with COVID-19 WHO CRF	-Yes, but not present anymore
	-Yes, still present
	-Yes, intermittent
	-No
	-Unknown
Fatigue Numerical Rating Scale Fatigue Severity Scale	Likert Scale from 1 to 7
	Likert Scale from 0 to 10
Modified Medical Research Council (MRC) Dyspnoea Scale	Likert Scale from 0 to 4
Comorbidity relapse or new comorbidity	-Yes
	-No
	-If yes, type of comorbidity and date of diagnosis
Hospital re-admission	-Yes
	-No
	-If yes, reason and date of re-admission
QoL (EQ5D-5L)	Likert scale from 1 to 5
	Scale from 0 to 100
Hospital Anxiety and Depression Scale (HADS-A/D)	Score Depression from 0 to 21
	Score Anxiety from 0 to 21
	(0–7 normal, 8–10 borderline, 11–21 patological)
Post Traumatic Stress Disorders (PTSD) checklist for DSM-5 (PCL-5)	Score from 0 to 80
Montreal Cognitive Assessment (MOCA)	Score from 0 to 30 (adjusted for age and education) (≥ 26 no cognitive impairment; < 26 cognitive impairment
Functioning (WHODAS)	Score from 0 to 100

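### The pulmonary work-up rule uses dyspnoea grades 2–5 on a scale collected as 0–4, and the study flowchart ties lung-function tests to saturation alone, so the article gives two conflicting rules for who is tested

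*Protocol article*

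**What the plan says.** The section on patient assessment and follow-up states that "patients undergo the MRC dyspnoea scale and oxygen saturation measurement at each post-COVID visit". It then gives the rule for going further: chest CT, the two lung-function tests (DLCO and spirometry) and a full pneumology assessment "will be performed if oxygen saturation is < 95% or MRC dyspnoea scale grade is 2–5". The rule has two alternative criteria, and either one is enough.

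Table 1, the study flowchart, lists the Modified MRC scale at T1, T2 and T3. Its legend, like that of Table 2, expands the short name of the MRC scale as the Modified MRC. Table 2 gives its range as "Likert Scale from 0 to 4".

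The lung-function rows of Table 1 read "If abnormal SO2, DLCO" and "If abnormal SO2, spirometry". Both are marked at T1 and T3 only, and neither mentions dyspnoea. The next row, for the pneumology visit, is marked at all three visits and allows clinical indication as well as abnormal saturation.

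The relevant secondary objective begins "To evaluate the long-term residual organ impairment". It names the lung first among four organ systems, and relates impairment to patient characteristics, disease severity and virology.

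**The concern.** A threshold has to be written on the scale it is applied to. Here the upper limit lies outside the collected scale, which also puts the lower limit in doubt. The lower limit decides who is tested.

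The second problem does not depend on the first. The text and the flowchart use different criteria for the same two tests: one accepts dyspnoea as sufficient, the other does not list it.

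The stake is the lung part of the organ-impairment objective. DLCO and spirometry results exist only for patients who were sent for them, so the trigger determines both the denominator and the mix of patients in it. If the two rules were applied in different places or at different times, an association between impairment and, say, variant or severity could partly reflect the testing rule. The inverse probability weighting in the data analysis section would not correct this. It models whether a hospitalised patient enters the post-COVID cohort, not whether someone who attends is sent for lung tests.

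**Working it through.** The documents give no figure to reproduce here, so the check sets the passages side by side.

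**Step 1: scale range.**
- Grades named in the trigger (text): {2, 3, 4, 5}.
- Grades available (Table 2): {0, 1, 2, 3, 4}.
- Overlap: {2, 3, 4}. Grade 5 cannot be recorded.

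Two different instruments cannot explain the mismatch, because the legends of Tables 1 and 2 equate the two names.

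**Step 2: what the trigger could mean on the collected scale.**
- Reading A, literal: grades 2–4 qualify.
- Reading B, written for five levels numbered 1–5 (an assumption; the article does not mention such a scale): collected grade = written grade − 1, so 2–5 becomes 1–4.

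The readings differ only for patients scoring 1.

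**Step 3: text against Table 1 for DLCO and spirometry.** Table 1 gives no number for abnormal saturation. I take it to be the text's < 95%, which is also an assumption. At T1 or T3:

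| Saturation | Grade (0–4) | Text, reading A | Text, reading B | Table 1 |
|---|---|---|---|---|
| < 95% | any | due | due | due |
| ≥ 95% | 0 | not due | not due | not due |
| ≥ 95% | 1 | not due | due | not due |
| ≥ 95% | 2–4 | due | due | not due |

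The rules agree in the first two rows. The last row is a conflict between text and table under either reading. The third row is a conflict only under reading B.

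**Step 4: size.** Let *a* be the share of attending patients with low saturation, *b1* the share with normal saturation and grade 1, and *b2* the share with normal saturation and grade 2–4.
- Share due under Table 1: *a*.
- Share due under the text, reading A: *a* + *b2*.
- Share due under the text, reading B: *a* + *b1* + *b2*.

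The text exceeds Table 1 by *b2* (reading A) or *b1* + *b2* (reading B). The article gives no distribution of saturation or dyspnoea grade, so none of the three shares is known and no number of patients follows.

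**Step 5: visits.** The text measures both trigger variables at every visit, while Table 1 leaves T2 blank for DLCO and spirometry. The text does not say outright that the tests are repeated whenever the trigger is met, so this is a gap to close rather than a firm contradiction.

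**The case against.** The strongest reply is that the mismatch may be harmless. Read literally, the rule selects grades 2–4, grade 5 is never reached, and nobody is misclassified. The doubt about grade 1 exists only if the rule was carried over from a 1–5 scale, and nothing in the article says so. That is correct, and a reader should not take a one-grade shift as established. What stands is that a rule naming an impossible grade leaves its own cut-point open to question.

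On the second conflict, it can be said that the text's list of tests is illustrative, that the same section also speaks of further evaluations as needed, and that a breathless patient with normal saturation can still reach a pneumology visit under Table 1. All true, so it would be too strong to say that such a patient could never have lung-function tests at a centre working from Table 1. But the text attaches a numeric condition to named tests, and Table 1 attaches a different one. The clinical-indication wording in the pneumology row is absent from the DLCO and spirometry rows, so the conflict remains.

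Some wider inferences are tempting but unsupported:
- **Bias by centre, country or wave.** Nothing shows that some centres follow the text and others the table, or that any such split tracks country or wave. Centres may also work from a fuller protocol and case report form that resolve the point. The inconsistency makes such bias possible; it does not establish it.
- **Untested patients counted as unimpaired.** No passage says this will be done.
- **Chest CT and ECG.** CT has no row in Table 1, but a condensed table may omit it. For the heart, the text says "Further evaluations such as an electrocardiogram, a cardiologic visit, and an echocardiography will be performed as necessary", while Table 1 marks the ECG at T1 without a condition. That is a real discrepancy, but it has no bearing on lung testing.

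**Conclusion.** The point holds as an internal inconsistency of moderate weight. Two things are certain from the article: grade 5 does not exist on the collected scale, and DLCO and spirometry have a saturation-or-dyspnoea trigger in the text but a saturation-only trigger in Table 1. Patients with normal saturation and a qualifying dyspnoea grade are due these tests under one rule and not under the other.

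Two assumptions enter. Doubt about patients scoring 1 requires that the rule was written for a 1–5 scale. The row-by-row comparison takes abnormal saturation in Table 1 to mean below 95%. The text-versus-table conflict over dyspnoea does not need the first.

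The number of patients affected cannot be computed from the documents. The consequence is confined to the lung component of one secondary objective. A reader might infer that the primary results are at risk, but incidence and risk factors rest on the WHO symptom-based definition, which does not use these tests. Nor would reconciling the rules make the tested group representative: under either rule, lung function is measured in a selected subgroup.

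**What to change.** Reconcile the assessment section with Tables 1 and 2 so that there is one trigger rule, expressed on the 0–4 scale actually collected, with one list of tests and one set of visits. The clinical threshold, and whether dyspnoea alone is sufficient, are for the sponsor to decide.

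Two additions would make the lung results interpretable. Record for each test which criterion triggered it (saturation, dyspnoea grade or clinical indication). Report lung impairment with both the number eligible under the rule and the number tested.

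The cost is a protocol clarification sent to the centres, one additional case report form field, and tagging of data already collected by the rule in force when the patient was seen. Sample size and the primary analysis do not change.

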Legend: WHO CRF, WHO’s Post COVID case report form (constitutional, respiratory, cardiac, neurological, digestive, muscoloskeletal, ear/nose/throat, psychological, psychiatric symptoms; dermatologic, renal, endocrine, haematologic, autoimmune manifestations); MRC dyspnoea scale, Modified Medical Research Council Dyspnoea Scale; QoL (EQ5D-5L), quality of life (5-level EQ-5D version); MOCA, Montreal Cognitive Assessment; HADS-A/D, Hospital Anxiety and Depression Scale; PCL-5, Post Traumatic Stress Disorders (PTSD) checklist for DSM-5; WHODAS, World Health Organization Disability Assessment schedule 2.0, 12-item version

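### Organ tests done only on a trigger cannot carry the organ-impairment objective, and no dedicated peripheral-nerve measure is named

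*Protocol article*

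**What the plan says.** Under Study objectives, one secondary objective is "To evaluate the long-term residual organ impairment, specifically of the lung, heart, central nervous system, and peripheral nervous system", in relation to age, gender, comorbidities, disease severity, variant, mutations and viral load.

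The section Patient assessment and follow-up protocol, with Table 1, sets who is tested:

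- **Heart.** The text says "Further evaluations such as an electrocardiogram, a cardiologic visit, and an echocardiography will be performed as necessary". Table 1 has the row "If cardiac symptoms, echocardiogram" at T1 and T3, and a cardiology visit on cardiac symptoms and/or clinical indication. Table 1 also lists an ECG at T1 with no condition attached.
- **Nervous system.** Table 1 has "If abnormally MOCA and/or clinically indicated, neurology visit" at all three visits; the text says "Patients will be referred to a psychologist or a neurologist as necessary".
- **Lung.** The text makes CT, DLCO, spirometry and a pneumology evaluation depend on low oxygen saturation or the MRC dyspnoea grade. Table 1 makes DLCO and spirometry depend on abnormal saturation only.

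Other measures have no trigger. The text lists "HADS-A/D, PCL-5, and MOCA, which will be performed at each scheduled visit". Oxygen saturation, the dyspnoea scale, the WHO CRF, and new comorbidity or re-admission are also scheduled at every visit. The legend to Table 2 shows that the WHO CRF covers "constitutional, respiratory, cardiac, neurological, digestive" and further symptom domains. Patients who cannot attend may complete the questionnaires by phone.

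**The concern.** The objective asks how organ impairment varies with exposures such as severity, age and comorbidity. The tests that detect impairment go mainly to patients with symptoms, an abnormal screening result or a clinical indication. Symptoms can arise from organ damage, but also from the exposures themselves. An analysis among tested patients then conditions on a common effect of exposure and impairment. Its frequencies describe the tested, and its associations can shrink, vanish or reverse.

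The Data analysis section recognises collider bias, but only for attendance at the post-COVID visit. The peripheral nervous system is named in the objective, yet the article names no instrument dedicated to it.

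**Working it through.** The article states no rate, effect size or power for organ impairment, so there is no figure to reproduce. The check has two parts: who is measured, and how large the distortion could be on assumed inputs.

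**1. Who is measured**

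| Organ | Scheduled without a trigger | Only on a trigger or indication |
|---|---|---|
| Lung | Oxygen saturation, dyspnoea scale, WHO CRF | DLCO, spirometry, CT, pneumology visit |
| Heart | Heart rate, blood pressure, WHO CRF; ECG at T1 by Table 1 but not by the text | Echocardiography, cardiology visit |
| Central nervous system | MOCA, WHO CRF | Neurology visit |
| Peripheral nervous system | WHO CRF neurological symptoms, general medical visit | Neurology visit, whose one named trigger is a cognitive score |

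**2. What the planned methods cover.** The weights are the inverse probability that a hospitalised patient enters the post-COVID cohort. They do not model who, within that cohort, receives an organ test. The missing-data methods named (missing indicator or multiple imputation) do not fill the gap: an indicator does not remedy an unmeasured outcome, and imputing a test result for patients who met no trigger has little observed support.

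**3. Frequency (assumed inputs).** Let π be true impairment, a the probability of the trigger in impaired patients, and s that in unimpaired patients.

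Frequency among tested = πa / [πa + (1 − π)s]. Detected among all attendees = πa.

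With π = 10%, a = 60%, s = 20%: tested = 0.06 + 0.18 = 24%; frequency among tested = 0.06/0.24 = 25%; detected among all = 6%. The truth is 10%. Over π 5–20%, a 40–80% and s 10–30%, the tested-only figure runs from 6.6% to 66.7%, and the all-attendee figure from 2% to 16%.

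**4. Association among tested patients (assumed inputs).** True impairment is 20% in hospitalised patients and 10% in outpatients, a risk ratio of 2.0; a = 60% in both.

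| s, hospitalised / outpatient | Impaired among tested | Ratio |
|---|---|---|
| 30% / 20% | 0.12/0.36 = 33% v 0.06/0.24 = 25% | 1.33 |
| 30% / 10% | 0.12/0.36 = 33% v 0.06/0.15 = 40% | 0.83 |
| 40% / 10% | 0.12/0.44 = 27% v 0.06/0.15 = 40% | 0.68 |

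On the odds-ratio scale, the tested-only value is the true OR × (a₁/s₁)/(a₀/s₀), with 1 for exposed and 0 for unexposed. If the trigger depends on impairment alone, a true OR of 2 stays 2.0. With a = 60% in both groups and s = 30% v 20% it is 2 × (2/3) = 1.33; with 40% v 20% it is 1.00. Under the same shifts a true OR of 1 becomes 0.67 or 0.50. The bias can also run upward: with a = 70% v 50% and s = 20% in both, a true OR of 1 becomes 1.4.

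**5. All-attendee denominator (same true ratio of 2.0).** With a = 60% in both groups, 0.12/0.06 = 2.0. With a = 70% v 50%, (0.20 × 0.70)/(0.10 × 0.50) = 0.14/0.05 = 2.8. With a = 50% v 70%, 0.10/0.07 = 1.43. This denominator removes the dependence on s but not on a.

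**The case against.** The strongest reply is that no sentence commits the sponsor to analysing organ impairment among tested patients only. The organ-specific analysis and its denominator may stand in the full protocol or analysis plan, and their absence from an article is no fault. That stands, so the tested-only bias is a hazard of the design and not a stated analysis. What a later plan cannot do is recover test results from patients who were never referred; the testing rules are fixed here.

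A reader might go further and infer that the whole objective is answered in a sample selected on its own outcome. The documents do not support that. MOCA, saturation, dyspnoea, the WHO CRF and new comorbidity (with type and date) are scheduled for everyone. Selection for the conditional tests is on symptoms, screening results or clinical indication, which are proxies for impairment. Nor are untriggered patients shown to have no chance of evaluation, because the specialist visits carry a clinical-indication route.

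A reader might also infer that nothing captures peripheral nerves. Neurological symptoms are recorded in all, a neurology visit could detect neuropathy, and the supplementary CRF is not shown. Only the absence of a named, dedicated measure is supported.

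Finally, an all-attendee denominator is not a cure: the ratio of 2.0 that it returns depends on equal symptom probability among the impaired.

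**Conclusion.** The point holds in limited form. Echocardiography, DLCO, spirometry, CT and the specialist visits are conditional. Their results do not give cohort frequencies, and risk-factor associations estimated among the tested are biased when the exposure also drives symptoms. On the assumed inputs a true risk ratio of 2.0 becomes 0.68 to 1.33. These sizes are illustrations; the article supplies no rates, and the odds ratio is undistorted if testing depends on impairment alone. The attendance weights do not address this selection.

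For the peripheral nervous system, the article supports a symptom-based component and no more. Two contradictions need no assumptions: the ECG is unconditional at T1 in Table 1 but performed as needed in the text, and the DLCO/spirometry trigger includes the dyspnoea grade in the text but not in Table 1.

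**What to change.** 1. For associations with severity, variant, viral load and patient factors, take as main measures those scheduled for every participant: MOCA, the dyspnoea scale, the cardiac and neurological domains of the WHO CRF, and new comorbidity or re-admission. Use oxygen saturation, heart rate and blood pressure in clinic attendees only, because phone follow-up cannot be assumed to supply them.
2. Report conditional-test results as clinically detected impairment, with all clinic attendees at that visit as the denominator. Do not estimate risk-factor associations among tested patients only. State that the all-attendee figure remains open to differential ascertainment when symptom reporting among the impaired differs by exposure.
3. Restate the peripheral nervous system component as WHO CRF neurological symptoms, unless the full CRF holds a dedicated measure; if it does, name it.
4. Reconcile the text with Table 1 on the ECG and on the DLCO/spirometry trigger. Which rule applies is for the sponsor to state.

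The cost is wording and denominators; no test is added. The claim narrows from residual organ damage to clinically detected impairment plus screening measures and symptoms, and subclinical damage is not estimated.
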